## 2. Original Study Protocol Methods

### 2.1. Study Design

This study is a two-armed, parallel group cluster RCT that will be executed in six European countries (Italy, Slovenia, Sweden, Switzerland, the Netherlands and United Kingdom). Cluster randomization is used to minimize contamination between intervention and control arms [61]. Indeed, if randomization were performed at the individual participant level, there would be a risk for exchange of information between AYCs within the same cluster. Clusters will consist of AYCs attending the same school (in Slovenia, Sweden and Switzerland) or living in the same geographical area (i.e., neighborhood or post-code area) (in Italy, the Netherlands and the United Kingdom). Clusters will be randomly assigned to either the ME-WE intervention or the waitlist control (1:1 allocation ratio), so that all eligible participants from the same school or geographical area are in the same study arm. Randomization will be conducted by a research member who is neither involved in the recruitment nor in the intervention delivery, using an online number generator. To achieve a certain degree of blinding, both schools and community-based service organizations (for geographical area clusters) and participating AYCs will be informed that the study aims to investigate the effects of different support strategies on AYCs’ well-being. They will not be told which condition they have been allocated to, nor will they be offered detailed information about the respective other trial arm during the study. Outcomes will be measured at the individual level. Both the ME-WE intervention and the waitlist control group will be assessed at baseline (T0), immediately post-intervention for the ME-WE intervention group or after 7 weeks for the waitlist control group (T1), and at a 3 months follow-up (T2). Participant-reported outcome measures will be used. Trial data analysts will be blinded to group allocation. After the 3 months follow-up the waitlist control group will receive the same program as the intervention group. The consolidated standard of reporting trials (CONSORT) 2010 statement extended to cluster trials is followed in this study [62]. The research flow diagram is presented in Figure 1. This protocol is based on the SPIRIT (standard protocol items: recommendations for interventional trials) guidelines [63] and has been registered at clinicaltrials.gov (accessed on 22 September 2019, trial registration number: NCT04114864).

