### 2.7. Sample Size Calculation

For the primary outcome variables, a moderate effect size (*f* = 0.25) was pursued based on previous evidence in RCTs using ACT-based interventions [56,84,112]. A minimum group size of 24 AYCs was established based on power analyses with a power of 80% and an α-error probability of 5%. However, in the case of cluster RCTs, an effective sample size is in fact lower than that suggested by the actual number of participants due to observations on participants in the same cluster tending to be correlated [62]. Thus, initial sample size estimation (performed as if randomization occurred at the individual level) was corrected taking into account randomization occurring at the cluster level. For each country, an average cluster size was estimated using the formula for sample size determination in a finite population [113] and assuming the prevalence rate of AYCs in the population of adolescents aged 15–17 in that country. Based on available data, the estimated prevalence rate of YCs is about 3% in Italy [114], 7% in Sweden [115], about 8% in Switzerland [3], 6% in the Netherlands [116] and in the United Kingdom approximately 7% of all children are engaged in a high amount of caring and 3% in a very high amount [117], while no estimation is available yet for Slovenia. As Italy and Slovenia have both been classified as countries at the initial stage of awareness concerning AYCs [118], the Italian prevalence rate was also applied in the Slovenian sample size calculation. A design effect was then calculated using the average cluster size and an assumed intracluster correlation of 0.05. This design effect was multiplied by the initial sample size to obtain a sample size corrected for the cluster-based design, which was further increased by 20% to compensate for attrition. The minimum total sample sizes obtained from this procedure were as follows: 80 AYCs (40 AYCs in the intervention and 40 AYCs in the waitlist group) in Italy and Sweden, 76 AYCs (38 AYCs in the intervention and 38 AYCs in the waitlist group) in Slovenia, 102 AYCs (51 AYCs in the intervention and 51 AYCs in the waitlist group) in Switzerland, 112 AYCs in the Netherlands (56 AYCs in the intervention and 56 AYCs in the waitlist group) and 142 AYCs (71 AYCs in the intervention and 71 AYCs in the waitlist group) in the United Kingdom.

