### 2.8. Statistical Analyses

Statistical analyses will be performed at both national and cross-national levels. Data will be analyzed using intention-to-treat principles [119] and adjusted for cluster effect [62]. Baseline characteristics will be preliminarily compared to check equivalence between study groups using analysis of variance (ANOVA) and *χ*^2^ tests. To answer primary and secondary research questions, differences in primary and secondary outcomes between the study arms from T0 through T1 and T2 will be tested using linear mixed effect models. These analyses will be based on individual participant-level data, allowing for clustering between AYCs within the same school or geographical area [62,120]. Models will include the fixed effects of study arm, country and delivery approach, time and their interaction effects. The cluster will be considered as a random effect. Models will be adjusted for characteristics that are unbalanced between study arms and significantly associated with the outcome measures. In case of violations of assumptions underlying planned analyses (e.g., equal variance and normal distribution of residuals) appropriate mathematical transformations of raw scores (e.g., logarithmic scale) or robust estimation methods will be applied [121]. Interpretation of results will be based on both statistical significance (*p* < 0.05, two-tailed) and measures of effect size [122]. We will also summarize post-intervention self-assessment and process evaluation measures. Analysis of qualitative data in national languages (for control variables likes and dislikes about caring and for intervention acceptability) will be performed using content analysis [123].

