### 3.6. Statistical Analyses Amendments

For countries that turned to an individual-based RCT (i.e., Sweden and Switzerland), statistical analyses will be performed at the individual participant-level, with no cluster-based adjustment. Statistical analyses at the cross-national level will be performed separately for countries conducting cluster RCTs (i.e., Italy, Slovenia, the Netherlands and United Kingdom) and countries conducting individual-based RCTs (i.e., Sweden and Switzerland). For individual based RCTs, differences in primary and secondary outcomes between the study arms from T0 through T1 and T2 will be tested using mixed ANOVA. Models will include the effects of study arm, country, time and their interaction effects. In case of violations of assumptions underlying planned analyses, appropriate data transformations or robust estimation methods will be applied [121]. Analysis of qualitative data collected using newly added COVID-19-related open-ended questions in national languages would be performed using content analysis [123].

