## 4. Trial Status

The recruitment of participants started in May 2019. Randomization began in September 2019, and the first baseline assessment was completed on 24 October 2019. Before COVID-19-related amendments (April 2020), a total of 98 AYCs was recruited. The trial is currently ongoing. Preliminary data available from Italy (*n* = 22, October 2019–March 2020) indicated feasibility of the ME-WE trial and acceptability of the ME-WE intervention. The proportion of eligible AYCs (screened between May and September 2019) who participated in the trial was 84%. Seventy-three percent of AYCs in the intervention group attended at least 70% of intervention sessions. Twenty-eight percent of all participants were lost to follow-up. Responses of AYCs in the intervention group to the post intervention self-assessment indicated that participants had a clearer vision of their thoughts, took better care of themselves and were generally satisfied with and enjoyed the intervention.

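### The amended cross-national analysis is split by unit of randomisation and never combined, so no planned estimate answers the single primary question with all six countries

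*Protocol article*

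**What the plan says.** The Introduction poses the primary research question once, as intervention against control, with no limit by country or by unit of randomisation. The Discussion's limitations paragraph repeats the aim as a comparison of the whole intervention with the waitlist.

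Section 2.8 states: "Statistical analyses will be performed at both national and cross-national levels". Its linear mixed model has arm, country, delivery approach and time as fixed effects, with interactions, and cluster as a random effect.

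Section 3.1 moves Sweden and Switzerland to individual randomisation. Section 3.6 then states: "Statistical analyses at the cross-national level will be performed separately for countries conducting cluster RCTs". These are Italy, Slovenia, the Netherlands and the United Kingdom. Sweden and Switzerland form the second set and are analysed by mixed ANOVA. The article describes no pooled model, no meta-analytic combination and no rule for reading the two results together.

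The opening of Section 3 keeps Section 2 in force only where the amendments are silent. Section 3.6 is not silent on the cross-national analysis, so the six-country model of Section 2.8 is not carried forward. The Discussion presents the article as setting out the analysis plan, in order to avoid data-driven analysis.

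**The concern.** The trial will produce two cross-national answers to one question, each less precise than the data allow. If they differ in size or in significance, the plan contains no estimate that uses all the data. A pooled figure added after the two results are known would be the kind of data-driven choice that the article says it wants to prevent.

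The change in randomisation unit does not force this outcome. Both sets compare the same two arms, on the same core questionnaires, at the same three time points. The unit of randomisation determines how the variance of each set's effect must be estimated. It does not prevent the two effects from being combined.

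**Working it through.** **Inputs**
- Section 2.7: base size 24 per arm, 80% power, alpha 5%; "a moderate effect size (*f* = 0.25) was pursued".
- Section 2.7: "A design effect was then calculated using the average cluster size and an assumed intracluster correlation of 0.05". The cluster sizes themselves are not given. Attrition is allowed for by a 20% increase.
- Section 2.7 totals: Italy 80, Slovenia 76, the Netherlands 112, United Kingdom 142.
- Section 3.5: 58 for Sweden and Switzerland, read here as 58 in each.

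**Step 1: reproduce the plan's figure.** 24 × 1.2 = 28.8, rounded up to 29 per arm, or 58 in total. This matches Section 3.5 and supports the per-country reading, because 24 per arm was the base size for one country.

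**Step 2: simple form.** If each country supplies the equivalent of 24 independent adolescents per arm, the effective sizes per arm are:
- cluster set: 4 × 24 = 96
- individual set: 2 × 24 = 48
- six countries: 144

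The standard error is proportional to 1/√n, so the ratios to the six-country estimate are:
- cluster set: √(144/96) = 1.22
- individual set: √(144/48) = 1.73

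**Step 3: from the stated country totals.** Solving N/2 = 24 × DE × 1.2 for the design effect DE, and then DE = 1 + (m − 1) × 0.05 for the mean cluster size m:

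| Country | N/2 | DE | m |
|---|---|---|---|
| Italy | 40 | 1.39 | about 9 |
| Slovenia | 38 | 1.32 | about 7 |
| Netherlands | 56 | 1.94 | about 20 |
| United Kingdom | 71 | 2.47 | about 30 |

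Effective total N is the sum of N/(1.2 × DE):
- cluster set: 4 × 48 = 192. This follows by construction, since DE was solved from the 24 per arm.
- individual set: 116/1.2 = 96.7
- six countries: 288.7

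The standard error of a standardised difference is 2/√N: 0.144, 0.203 and 0.118. The ratios are 0.144/0.118 ≈ 1.23 and 0.203/0.118 ≈ 1.73 (from unrounded values). The cluster set holds about 66% of the information and the individual set about 34%.

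**Step 4: sensitivity.** With the cluster sizes of Step 3 held fixed:

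| Assumption | Cluster set | Individual set |
|---|---|---|
| Intracluster correlation 0 | 1.13 | 2.13 |
| 0.01 | 1.15 | 2.00 |
| 0.05 (plan) | 1.23 | 1.73 |
| 0.10 | 1.30 | 1.56 |
| 0.20 | 1.44 | 1.39 |
| 0.05, with 58 covering both countries together | 1.12 | 2.23 |

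A loss rate common to all countries, such as the 28% reported from Italy in Section 4, leaves the ratios unchanged.

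**The case against.** The strongest reply is that a six-country effect was never the stated target. Sections 2.7 and 3.5 size each country for its own 80% power, and national analyses remain in place. The model in Section 2.8 includes interactions with country, so even that plan did not promise one overall number. This stands as a limit. The loss is one of precision relative to a combined estimate, and no stated power target is missed. It does not explain why a single question should have no planned overall answer.

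A second reply is that the sets differ in more than randomisation. Sweden and Switzerland turn to national social-media recruitment (Section 3.2). Under Section 3.3 both use the app, while Italy, Slovenia and the United Kingdom do not. Separate reporting is therefore reasonable. However, the Netherlands also uses the app and is analysed with the cluster set, so the split does not follow delivery mode. These differences call for a heterogeneity check and do not rule out an overall estimate.

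A third reply is that the two estimates can be combined later, or that this can be left to a fuller plan. The data are indeed not lost. But Section 3.6 states a choice on exactly this matter, and combining after the results are seen would not be prespecified.

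The documents do not support two stronger readings that a reader might infer:
- **That the two sets will often disagree on significance.** Putting 24 per arm per country into a plain two-sample t-test suggests this. That is not the plan's test: at 24 per arm and d = 0.5 (two groups, *f* = 0.25) it has about 40% power, not the stated 80%. In a repeated-measures arm-by-time test set to give 80% at 24 per arm, disagreement at the planned effect occurs in about 2% of trials. The rate rises for smaller effects, but the documents give no basis for choosing one.
- **That recruitment has fallen short and makes the loss worse.** Section 4 says "Before COVID-19-related amendments (April 2020), a total of 98 AYCs was recruited", but this is an interim count in a trial described as ongoing. Section 5 speaks only of possible difficulty in reaching the target.

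**Conclusion.** The point holds as a gap in the cross-national analysis. Section 3.6 replaces one six-country analysis with two disjoint ones and plans no combination, while the primary question is a single comparison. The standard errors are about 1.2 times (cluster set) and 1.7 times (individual set) that of a combined estimate.

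This rests on 24 effective adolescents per arm per country, an intracluster correlation of 0.05 and 58 per country. It also assumes no between-country heterogeneity and no clustering by intervention group in Sweden and Switzerland. The absolute standard errors are for an unadjusted comparison at one time point. Baseline adjustment would change them but leave the ratios roughly as they are. Some loss remains in each set across all the variations tried. The change should be made, but the trial's national analyses do not depend on it.

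**What to change.** In Section 3.6, before any unblinded analysis, prespecify one six-country estimate of the arm-by-time effect. The preferred route is to estimate the effect in each set with its own variance model, combine the two by inverse-variance weighting, and test heterogeneity between sets.

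An alternative is one linear mixed model with:
- country fixed effects;
- a participant random effect in all countries;
- a cluster random effect only in the cluster-randomised countries;
- an arm-by-time-by-set term.

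The two routes are not identical. Entering each individually randomised adolescent merely as a cluster of one, without a participant effect, would not be adequate. A single variance component would then stand for between-cluster variation in four countries and between-person variation in two.

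Keep the two set-level analyses as supportive results and leave the national analyses as they are. The cost is a few sentences and one more analysis, with no new data or participants. The small downside is the assumption that the sets are similar enough to combine, since recruitment route and app use differ partly between them. The heterogeneity test addresses this, within the limits of its power.

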### 2.5. Outcome Measures

Demographic (gender, age, country of birth, nationality, migration background, place of living, living conditions and family composition) and caregiving information (number and age of people cared for, type of relationship with the care recipient, nature of the illness or health condition of the care recipient and time since caregiving started) will be collected at baseline (T0). Primary and secondary outcomes and control variables will be collected at baseline (T0), post-intervention (T1) and 3 months post-intervention (T2). T0, T1 and T2 assessments in the ME-WE intervention group will be performed at the beginning of session 1, at the end of session 7 and at the beginning of session 8, respectively. Primary outcome variables will include psychological flexibility, mindfulness skills, resilience, subjective mental and physical health, general and caring-related quality of life, impact of caring and social support. Secondary outcome variables will be self-reported school/training/work experience, performance and attendance. The following variables will be used as control variables: caring activities, overall amount of caring, likes and dislikes of caring, formal support received and caring-related perceived social support. Both quantitative and qualitative data will be collected using a questionnaire available in both web-based and paper-and pencil versions. All selected standardized self-report measures were specifically developed and/or tested for use with adolescents. Measures not available in the local languages of participating countries have been translated after permission from the authors. The committee translation method was used [71]. Specifically, in non-English countries, two independent researchers fluent in English independently translated each measure from English into their local language, and then met to discuss eventual discrepancies and reach consensus on an integrated version. English questionnaires were used for participants in the United Kingdom. Ad-hoc developed items were formulated in English and then translated using the same procedure used for standardized tools. Participants in the intervention group will complete a post-intervention self-assessment tool at T1 and T2. Process evaluation outcomes will include feasibility, acceptability and fidelity indicators.

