## 5. Discussion

AYCs are at risk of adverse mental, social and educational outcomes that may continue into adulthood implying reduced psychosocial adjustment [5,9,10,11,18,19,20,24,25]. A primary prevention model has been recommended to mitigate against negative outcomes and foster transitions to adulthood [18,38,39,40]. To the best of our knowledge, this study will be the first RCT evaluating the efficacy of a primary prevention, group-based intervention for middle adolescents who care for a family member or significant other in Europe. Noteworthy, participatory codesign, user-centered principles were followed in the development of the ME-WE intervention. In all participating countries, YCs, former YCs and professionals working in the field of youth and/or caring participated in BLNs aimed to collect expert knowledge for the designing of a support program tailored to AYCs’ needs and preferences, with expected favorable effects on participation, adherence and the likelihood of the program success. The components of DNA-V included in the ME-WE intervention promote skills to manage difficult emotions and thoughts, identify values and derive values-oriented goals, develop strengths, build positive social networks and achieve psychological flexibility and mindfulness [49]. The ME-WE intervention has the potential to prevent maladjustment and promote well-being and healthy development in AYCs by building resilience through the skills learnt to be flexible in facing life events, including caring-related ones, and live according to personal values. We anticipate improvements in protective factors targeted by the ME-WE intervention. Specifically, we expect that, compared to the waitlist control group, ME-WE intervention participants will report greater improvements in psychological flexibility, mindfulness, resilience, subjective health and quality of life and in perceived emotional impact of caring and social support, and that these effects will be maintained at the 3 months follow-up. We will also explore potential changes in self-reported school, training or work experience, performance and attendance, which are considered as secondary outcomes because the ME-WE intervention does not address these variables directly. This international RCT has received formal ethical approval and is now being implemented. On completion, results will be reported as outlined in the CONSORT statement [129] and will be published in subsequent peer-reviewed scientific publications, presented at national and international conferences and widely disseminated to professionals, decision makers, policy makers and civil societies at regional, national and international levels. In this article we also detailed the statistical analysis plan to ensure analytical transparency and avoid data-driven analyses [130,131].

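### No contrast or time point is tied to the claim of maintained benefit, and the three-wave arm-by-time test cannot support it and has less power than a baseline-adjusted contrast

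*Protocol article*

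**What the plan says.** Section 3.6, for the individually randomised countries: "differences in primary and secondary outcomes between the study arms from T0 through T1 and T2 will be tested using mixed ANOVA". The terms are listed next: "Models will include the effects of study arm, country, time and their interaction effects".

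Section 2.8, for the cluster countries, says that differences "between the study arms from T0 through T1 and T2 will be tested using linear mixed effect models", and "Models will include the fixed effects of study arm, country and delivery approach, time and their interaction effects". The cluster is a random effect. Covariate adjustment is planned only for characteristics that are both unbalanced between arms and associated with the outcome.

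Section 2.5: outcomes "will be collected at baseline (T0), post-intervention (T1) and 3 months post-intervention (T2"). In the intervention arm the three assessments "will be performed at the beginning of session 1, at the end of session 7 and at the beginning of session 8, respectively", so T0 precedes treatment.

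Section 5 states the expected result: greater improvement than the waitlist on the primary measures, "and that these effects will be maintained at the 3 months follow-up". It adds that the article sets out the statistical analysis plan so that analyses are not data-driven.

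**The concern.** The hypothesis has two parts: the intervention arm improves more, and the gain is still there at 3 months. In a model with arm, time and their interaction, differential change is carried by arm-by-time. The arm main effect does not help, because it averages in the pre-treatment wave. With three categorical waves, the null of the interaction is that the two arm profiles are parallel. It is not that there is no benefit at T2. A benefit that has gone by T2 and one that has lasted both break that null, and a significant result does not say which occurred.

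Two things are at stake. First, the step from a significant interaction to a statement about maintenance is left open, so it would have to be chosen after the data are seen. Second, using T0 as an outcome level instead of a covariate, and spending two degrees of freedom on a one-directional hypothesis, gives up power. Section 4 reports 28% loss to follow-up in the early Italian data against the 20% planned, and Section 5 anticipates difficulty in reaching the target sample.

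**Working it through.** **Inputs from the article.** Three waves; two-sided alpha 0.05 (Section 2.8); f = 0.25 (Section 2.7); 24 per arm for 80% power, raised to 29 per arm for 20% attrition (Section 3.6's companion, Section 3.5). Sections 2.7 and 3.5 do not say which effect f refers to, and no between-wave correlation rho is given.

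**Assumptions.** Compound symmetry, unit SD, rho from 0.3 to 0.8, no missing data, no clustering. The main effect size is d = 0.5 SD, which is f = 0.25 for a plain two-group comparison.

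**Reproducing the 24 per arm.** The within-between interaction formula is lambda = f² × m × N/(1 − rho), with df (m − 1) and (m − 1)(N − 2). With m = 3, N = 48 and rho = 0.1, lambda = 0.0625 × 3 × 48/0.9 = 10.0 and power is 80.2%, so exactly 24 per arm. This match is conditional on rho: values of 0, 0.3 and 0.5 give 27, 19 and 14 per arm. A two-sample comparison at d = 0.5 would need 64 per arm. Attrition: 24 × 1.2 = 28.8, rounded up to 29.

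**Step 1: same power for a lasting and a vanished effect.** With n per arm, the arm-by-time noncentrality is lambda = (n/2) × SS/(1 − rho), where SS is the sum of squared deviations of the three arm differences from their mean.
- Lasting profile (0, d, d): mean 2d/3, SS = 4d²/9 + d²/9 + d²/9 = (2/3)d².
- Vanished profile (0, d, 0): mean d/3, SS = d²/9 + 4d²/9 + d²/9 = (2/3)d².

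Both give lambda = n × d²/[3(1 − rho)]. At n = 24, d = 0.5, rho = 0.5 this is 24 × 0.25/1.5 = 4.0, and power is 40.4% for each (simulated 40.6% and 40.7%). The equality is exact only under compound symmetry. With AR(1) correlation 0.7, the univariate F rejects 50% (lasting) against 55% (vanished), and a multivariate test 49% against 73%.

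**Step 2: power for a sustained effect.** The comparator is the mean of T1 and T2 adjusted for T0. Its residual variance is (1 + rho)/2 − rho², and lambda = (n/2) × d²/[(1 + rho)/2 − rho²] on 1 df. At rho = 0.5: 12 × 0.25/(0.75 − 0.25) = 6.0, power 67%.

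n = 24 per arm, d = 0.5:

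| rho | arm-by-time, 2 df | T0-adjusted T1/T2 mean, 1 df | gain, points |
|---|---|---|---|
| 0.3 | 30% | 62% | 32 |
| 0.5 | 40% | 67% | 27 |
| 0.6 | 49% | 72% | 23 |
| 0.7 | 62% | 81% | 19 |
| 0.8 | 80% | 91% | 11 |

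With Sweden and Switzerland pooled (48 per arm), the comparison is 71% against 93% at rho 0.5; the gain is 15 points at rho 0.6 and 7 at rho 0.7.

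**Step 3: where the 27 points at rho = 0.5 come from.** A 1-df contrast of the T1/T2 mean minus T0, taken from the planned model, has variance factor (1 + rho)/2 + 1 − 2 × rho = 1.5(1 − rho) and lambda = 3/0.75 = 4.0, the same as the omnibus test. Using 1 df instead of 2 lifts power from 40% to about 50%. Adjusting for T0 instead of subtracting it lifts it from about 50% to 67%. So about 10 points come from the contrast and about 17 from the adjustment.

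**Step 4: other readings.** If f = 0.25 is the interaction effect, then equating 0.0625 × 3 × 48 = 9 with 24 × d²/3 = 8d² gives d² = 1.125, d = 1.06. At 24 per arm the gain is then about 10 points at rho 0.3 (89% to 99.8%) and 3 at rho 0.5 (97% to 99.9%). With d = 0.3 the gain is 13 to 15 points; with d = 0.8 and rho = 0.5 it is 16.

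**The case against.** The strongest reply has four parts.

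1. A reader might infer that rejecting for an effect present only at T1 is a false positive. It is not. The research question at the end of the Introduction asks about favourable change over the whole study period, and a real T1 benefit makes that null false. What stands is narrower: such a rejection does not show maintenance.

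2. A reader might infer that the plan loses more than 20 points of power. The article does not support a fixed figure. It gives no rho and does not define f. At d = 0.5 the gain falls below 20 points by rho 0.7 with 24 per arm, and by rho 0.6 with 48. Wherever the planned test does have its stated 80% power, no alternative can gain more than 20. The gain also depends on the comparator: at rho 0.5, the T0-adjusted T2 difference alone gains only about 10 points (40% to 50%).

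3. A reader might infer that the omnibus interaction is the sole decision test. Neither Section 2.8 nor Section 3.6 says so; effect sizes also enter the interpretation, and follow-up contrasts may be set out in an analysis plan not shown here. This limits the point. Still, Section 5 presents the article as giving the analysis plan, and it names the model and terms without linking any contrast to the maintenance hypothesis.

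4. The linear mixed model in Section 2.8 can yield separate T1 and T2 contrasts, and the article does not say that time is categorical there. With linear time the equality in step 1 would not hold. The equality also needs compound symmetry; in the AR(1) 0.7 case checked, the departure favours the vanished effect.

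**Conclusion.** The point holds in a limited form. Sections 3.6 and 2.8 treat a pre-treatment score as an outcome wave and fix no contrast or time point for the maintenance hypothesis in Section 5. With categorical time, a significant arm-by-time test cannot on its own support that hypothesis; this needs no assumed effect size or correlation. Equal power for lasting and vanished effects does require compound symmetry.

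The efficiency loss is real, but its size is conditional: about 11 to 32 points at d = 0.5, 24 per arm and rho 0.8 down to 0.3, and about 10 points or fewer at rho 0.3 to 0.5 if f = 0.25 is the interaction effect. These figures ignore clustering and missing data. The change is worth making because it is cheap and the article describes the trial as still running.

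**What to change.** Model T1 and T2 as the outcomes, with the participant's own T0 score on that measure as a covariate. Include arm, wave, arm-by-wave and country, a repeated-measures covariance and, in the cluster countries, the cluster effect. Then state three rules:

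- Greater improvement is tested by the 1-df arm effect averaged over T1 and T2.
- Maintenance is claimed only from the T0-adjusted arm difference at T2, with its 95% CI.
- The omnibus arm-by-time test is descriptive.

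Apply this in both Section 2.8 and Section 3.6.

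The cost is analysis wording and code, plus one degree of freedom per model. Power falls for an effect present only at T1: about 22% against 40% at d = 0.5, rho 0.5 and 24 per arm. Reporting the T0-adjusted T1 difference as well would offset this.
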